**Table 1 Tab1:**
[figure not shown]
Overview of instruments

*S* Screening, *B* Baseline assessment; 3/6/9/12/15/18/21/24 = 3/6/9/12/15/18/21/24 months after start of the treatment phase, *6 FU* Follow-up at 6 months after end of treatment, *12 FU* Follow-up at 12 months after end of treatment, *BPDSI-5* Borderline Personality Severity Index, fifth edition, *BPD* Borderline personality disorder, *BSI* Brief Symptom Inventory, *DBT-WCCL* Dialectical Behavior Therapy-Ways of Coping Checklist, *DERS-18* Difficulties in Emotion Regulation Scale 18, *DERS-SF* Difficulties in Emotion Regulation Scale Short Form, *ECR-RS* Experiences in Close Relationships-Relationship Structures questionnaire, *EQ-5D-5L* 5-level EuroQol 5D version, *ISI* Insomnia Severity Index, *MHQoL-7D* Mental Health Quality of Life seven-dimensional Questionnaire, *NFQ* Nightmare Frequency Questionnaire, *ORS* Outcome Rating Scale, *SCID-5* Structured Clinical Interview for DSM-5, *SMI* Schema Mode Inventory, *WAI-S* Working Alliance Inventory-Short, *WHODAS 2.0* World Health Organization Disability Assessment Schedule 2.0

^a^The potential predictors of (differential) treatment response that are assessed only once at baseline are not included in this table

^b^A shortened version

^c^Including three to five idiosyncratic dysfunctional beliefs and one functional belief

^d^DERS-18 subscale ‘Awareness’

^e^Excluding the subscale ‘Awareness’

^f^Three versions of the ECR-RS will be assessed, measuring general attachment style and attachment styles with respect to two targets (i.e., most important therapist and group members)

^g^Two versions, measuring attachment styles with respect to two targets (i.e., most important therapist and group members), are assessed after the third group session

^h^SMI subscales Vulnerable Child, Angry Child, Impulsive Child, Detached Protector, Punitive Parent, and Healthy Adult

^i^Key characteristics of a promoting therapeutic environment (i.e., genuineness, safety, and equality) are assessed by 13 items formulated by ST experts

^j^Assessed after the third group session

All assessments are performed by trained local research assistants blind to the patients’ treatment condition, with exception of the SCID-5 interviews, demographic interview, and cost interview. The SCID-5 interviews can be administered by trained research assistants as well as trained intake staff members, both blind for condition. The demographic interview and cost interview contain questions on healthcare utilization and are therefore performed by non-blinded local research assistants. Due to the nature of the interventions, blinding of therapists and patients is not possible. All interviews, except for the SCID interviews, are audio-recorded. Participants receive financial compensation for their involvement in the study. Patients who discontinue their treatment or deviate from the treatment protocol will be encouraged to continue the assessments.

### Treatments

#### Format

For patients of both DBT and ST, treatment has a maximum duration of 25 months and starts with a pretreatment phase of approximately four weeks consisting of several (ST: ± three; DBT: ± five) individual sessions in which patients are prepared for the group sessions and become accustomed to their therapists and the treatment model. After the pretreatment phase, patients receive a combined program of individual sessions and group sessions (i.e., treatment phase). Group sessions of both treatments are offered in a semi-open format. If treatment slots are available, new patients can enter the ST group every 10 weeks and for DBT groups at the start of a mindfulness skills module. In DBT, the treatment phase has a maximum duration of 12 months and consists of weekly group sessions (i.e., skills training groups; 150 min), weekly individual psychotherapy sessions (50 min), and between-session consultation. The between-session consultation, often called telephone consultation although all kinds of technology can be used [95], is offered to the patient within limitations set by the individual therapist, varying between access to between-session support within working hours to 24/7 access to between-session support, which is officially the standard in DBT. In ST, the treatment phase has a maximum duration of 18 months consisting of weekly group (90 min) and individual (45 min) psychotherapy sessions for a period of 12 months, continued by weekly group psychotherapy sessions and biweekly individual psychotherapy sessions for a period of six months. Following the treatment phase, patients continue their treatment with a maintenance phase. The maintenance phase of DBT is a recently developed blended aftercare program with a maximum duration of 12 months. The blended aftercare program was developed based on results of previous studies (e.g., [31, 96]) and recommendations by several authors (e.g., [96–98]) to extend the duration of DBT to sustain or even enhance treatment effects. The DBT aftercare program consists of monthly individual psychotherapy sessions, three-monthly group sessions, and an eHealth intervention in which patients have online access to DBT handouts and worksheets [99]. The maintenance phase of ST consists of biweekly individual psychotherapy sessions for a period of three months, continued by three months of one individual session each month. Disregarding the time spent on telephone consultation, homework assignments, and eHealth, and based on 48 working weeks a year, patients will receive about 167 h of treatment if they follow the treatment protocol. Patients who have completed treatment successfully before they reach the maximum number of treatment sessions are allowed to complete treatment earlier, although the assessments will be conducted at the originally planned assessment points. Early termination of treatment requires substantial improvements in the primary and secondary outcomes and is decided in joint decision by the patient and therapist. The treatments are covered by the public health insurance. See Table 2 for an overview of the treatment formats.

**Table 2 Tab2:** Treatment formats

ST	Duration	DBT	Duration
Pretreatment phase	4 weeks	Pretreatment phase	4 weeks
Individual sessions		Individual sessions	
Treatment phase	18 months	Treatment phase	12 months
Weekly individual sessions	12 months	Weekly individual sessions	
Weekly group sessions		Weekly skills training groups	
Biweekly individual sessions	6 months	Telephone consultation	
Weekly group sessions			
Maintenance phase	6 months	Maintenance phase	12 months
Biweekly individual sessions	3 months	eHealth intervention	
Monthly individual sessions	3 months	Monthly individual sessions	
		Three-monthly group sessions	

Note. Early termination of treatment during the treatment phase or maintenance phase is permitted in case of successful recovery

#### Schema therapy (ST)

ST, developed by Jeffrey Young [22, 100], is based on an integrative cognitive model, combining cognitive behavior therapy and experiential techniques with insights from developmental theories, including attachment theory, and psychodynamic concepts [23]. Central concepts are early maladaptive schemas and schema modes. Early maladaptive schemas can be defined as broad, pervasive patterns of thoughts, emotions, memories, and cognitions regarding oneself and relationships with others, developed during childhood [22]. ST assumes that the frustration of core needs and early traumatic experiences lead to the development of early maladaptive schemas. A schema mode refers to an activated set of schemas and the associated coping response (i.e., overcompensation, avoidance, and surrender), and describes the momentary emotional, cognitive, and behavioral state of the patient. The following schema modes are characteristic of BPD [101]: 1) vulnerable child mode, associated with a fear of abandonment and strong emotions, such as loneliness, sadness, and helplessness, 2) angry and impulsive child mode, characterized by anger, frustration, hostility, and impulsivity, 3) punitive parent mode, representing the internalized voice of very punitive and critical attachment figures and associated with self-criticism, self-hatred, guilt, and self-denial, 4) detached protector mode, characterized by attempts to cut off the self from needs and feelings, resulting in symptoms of detachment, substance misuse, social withdrawal, and self-harm, and 5) healthy modes, reflecting in functional thoughts, cognitions, and behavior (i.e., healthy adult mode) and the feeling that core needs are been fulfilled (i.e., happy child mode). The first four modes are maladaptive schema modes and central to BPD. The last two modes are functional and often only weakly present at the beginning of the treatment [102]. Idiosyncratic schema mode models usually cover additional modes, depending on the specific problems and comorbidity of the patient.

ST aims to enable patients to fulfill their needs, reduce maladaptive schema modes, and strengthen adaptive schema modes. In this study, ST is offered in a combined group-individual format developed by Farrell and Shaw [103]. The group acts as an analogue of a family with the other patients as “siblings” and the two therapists as “parents” [103]. The group may speed up and amplify the effect of treatment by offering corrective emotional experiences, peer support, opportunities for in vivo practice, and a sense of understanding [104]. The individual ST follows the protocol as described by Arntz and Van Genderen [105].

#### Dialectical behavior therapy (DBT)

DBT is a comprehensive cognitive behaviorally based treatment for BPD, integrating strategies from cognitive and behavioral treatments, Zen-based acceptance strategies, and dialectical strategies [19, 106]. Linehan [19, 20] proposed a skills deficit model in which emotion regulation is central. More specifically, the model holds that the problematic behaviors associated with BPD (e.g., suicide attempts, self-injury, substance use) are in fact best understood as dysfunctional attempts to regulate emotions. Emotion dysregulation results from the complex transaction between dispositional emotional vulnerabilities and an adverse invalidating environment. Therefore, the treatment involves balancing problem solving strategies with loads of validation. DBT aims to help patients develop new skills, enhance motivation, ensure generalization of skills use, and change their environment if needed. In addition, DBT aims to enhance therapists’ motivation to deliver effective treatment [20].

DBT involves skills training groups, individual therapy, between-session consultation, and therapist consultation team meetings. DBT skills training groups teach patients behavioral skills in four different, yet inter-related, areas: mindfulness, interpersonal effectiveness, emotion regulation, and distress tolerance / radical acceptance. Individual therapy focuses on motivational issues and the acquisition and use of skills in daily life. A predetermined ordering of treatment targets is used in individual sessions and part of different stages of the treatment. Stage 1 focuses on stabilizing the patient and behavior control. Targets in this stage of the treatment include: life-threatening behavior, therapy-interfering behavior, quality-of-life-interfering behavior, and behavior skills. Stage 2 focuses on reducing posttraumatic stress and requires exposure to trauma-related cues [19]. Finally, Stages 3 and 4 target self-respect and the sense of incompleteness. However, due to time constraints, some patients might not enter all stages and most studies have focused on Stage 1 DBT [107]. Individual therapists provide between-session (telephone) consultation if needed. According to the guidelines of DBT, access to between-session consultation outside of office hours, preferably by the individual therapist, is part of DBT [19]. In this trial, between-session consultation by the individual therapist will be within limitations set by the therapist, which can vary between support provided within working hours to 24/7 access to telephone consultation. As access to between-session (telephone) consultation will vary between centers and individual therapists, the effect of therapist’s availability for between-session support will be examined. Finally, DBT therapists meet weekly in a DBT consultation team to motivate and support each other.

#### Therapists, training, and supervision

The therapists in this study will be licensed psychologists, psychotherapists, psychiatrists, or psychiatric nurses. Individual and group schema therapists must have completed a basic training in individual ST. Group schema therapists must have also completed a four-day training in the group schema therapy model of Farrell and Shaw [103]. All schema therapists receive a one-day training in experiential techniques by a certified ST trainer. DBT therapists are required to complete a three-day training in DBT and at least one member of the DBT team must have completed the 10-day intensive DBT training. In addition, DBT therapists receive a two-day kick-off training by certified DBT trainers to expand their knowledge of DBT. Moreover, DBT-therapists were given the opportunity to participate in a one-day training in imaginal exposure. According to Linehan [19], reducing behaviors and stress response patterns related to traumatic life events is a primary DBT target. Reducing posttraumatic stress is mostly part of Stage 2 of DBT and involves exposure to trauma-associated cues [19, 108]. However, some of the DBT therapists expressed concerns about their ability to apply the principles and procedures of exposure to treat traumatic memories in BPD patients. Therefore, the opportunity to participate in a one-day exposure training was offered to the therapists.

Before the start of the study, schema therapists should have received at least 10 individual supervision sessions by a licensed supervisor. There is no requirement for the minimum number of DBT supervision sessions. During the study, therapists receive supervision over a period of two years by certified supervisors. ST supervision is provided through teleconferencing biweekly in the beginning, then (two-)monthly after six to 12 months, depending on the experience of the therapists. DBT therapists receive supervision at location every three months. Moreover, there will be weekly DBT team meetings (i.e., DBT consultation team meetings) and biweekly ST team meetings. All individual ST sessions will be audiotaped, while individual DBT sessions and ST and DBT group sessions will be videotaped. These recordings are used for supervision and treatment adherence ratings. Treatment adherence, a component of treatment integrity (i.e., the extent to which a treatment is implemented as intended; [109]), refers to the extent to which the therapist utilizes prescribed techniques and procedures and avoids the use of proscribed techniques and procedures [110]. Adherence will be assessed in a random selection of session recordings by trained raters (master psychology students) blind for condition. Master psychology students will be trained by ST and DBT experts by using session recordings not used in the final adherence rating to practice with the instruments. Individual ST sessions will be rated on an adapted version of the Therapy Adherence and Competence scale for ST for BPD [111] and group ST sessions will be rated on the Group Schema Therapy Rating Scale – Revised [112]. Individual DBT sessions will be rated on the Dutch translation of the observer-rated version of the DBT Adherence Checklist for Individual Therapy [113]. An observer-rated instrument will be developed to assess the skills training groups.

#### Other treatment

During the treatment, patients are not allowed to engage in any other form of psychological treatment. However, in case of acute crisis, the crisis procedures of the treatments will be followed (e.g., telephone consultation by the therapist, contact a crisis line, visit the emergency room, hospitalization, individual crisis management sessions). Any additional treatment will be recorded and included in the analyses. Patients will only be withdrawn from the study at their request.

### Coronavirus disease (COVID-19) pandemic

This study is conducted during the COVID-19 pandemic. The pandemic is expected to have adverse effects on patients with mental health disorders [114]. In addition, in case face-to-face treatment is restricted in mental healthcare centers because of government and healthcare center policy, the treatment will be delivered via videoconferencing. Consequently, differences between patients will arise regarding the amount of treatment sessions delivered during the pandemic and/or via videoconferencing. We will control for a potential influence of the COVID-19 pandemic by, for example, adding dynamic regression parameters that include the impact of time in treatment during the pandemic. The definition of the indicator variable indicating the COVID-19 pandemic will be decided before start of the data-analyses (e.g., dummy variable indicating pandemic/no pandemic or continuous variable indicating the amount of time in treatment during the pandemic), given the unpredictability of the current situation. Moreover, exploratory analyses may be conducted to investigate the potential influence of the deviating treatment format (i.e., online vs. face-to-face individual sessions and/or group sessions) on the treatment effectiveness.

In addition, the assessments will be conducted via videoconferencing or phone, and the computer-based questionnaires will be completed by participants at home, if face-to-face assessments are not allowed. Before receiving the treatment and/or assessments via videoconferencing, patients will sign an additional informed consent form (see Additional file 2, Appendix B).

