This study has several other limitations that should be considered when evaluating the results. First, as power is conventionally set a 80% [84, 230–232], we used a minimum criterion of 80% power for the power analyses. However, this means that we accept a 20% chance of a false negative result. Second, since DBT and ST are both evidence-based treatments for BPD, differential effects in treatment outcome may be small or non-existing. To demonstrate equivalence or small effects between treatments, a very large sample size is needed. The sample size of the current study is not large enough (i.e., does not have ≥80% power) to reliably detect a small differential treatment effect. However, the comparison of treatments is not the main aim of the study. In addition, according to Luedtke et al. [233], a sample size of at least 300 patients per condition is required to have sufficient power for applying multivariable prediction models. Nonetheless, they also noticed that a smaller sample size might be justified if studies are designed to develop prediction models that can be tested in future studies. Moreover, the results of this study can contribute to building a database including trials on BPD that can be analyzed with meta-analytic techniques.

Second, this study does not include a no treatment control group, which might affect internal validity. When improvements are found in both treatments, but no significant differences between the treatments, the absence of a control group implies that it cannot be ruled out that non-specific factors such as attention or time (maturation) caused the improvements. However, including a control group receiving no treatment would clearly be unethical (e.g., patients are at risk of suicide). For similar reasons, it is not possible to standardize medication use and crisis management sessions. Any additional treatment or medication use will be monitored and included in the analyses.

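### Actual time in treatment during the pandemic is offered as an adjustment term, but it can depend on response, dropout and arm, so using it can bias the DBT–ST comparison

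*Protocol article*

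**What the plan says.** The COVID-19 section of the protocol article states that a possible pandemic influence will be controlled for. Its example of how is "adding dynamic regression parameters that include the impact of time in treatment during the pandemic". The variable itself is left open: "The definition of the indicator variable indicating the COVID-19 pandemic will be decided before start of the data-analyses", with the candidates given as "dummy variable indicating pandemic/no pandemic or continuous variable indicating the amount of time in treatment during the pandemic".

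Four other places bear on this:

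- **Format and Table 2.** Treatment lasts at most 25 months in both arms. A patient may finish sooner if the outcomes have improved markedly and patient and therapist agree. Assessments then still follow the original schedule.
- **Procedure and assessments.** Patients who stop treatment are asked to stay in assessment, so they remain in the data with a short time in treatment.
- **Statistical analyses.** The primary analyses follow intention to treat (randomised and at least one session). The methods described are labelled examples, and an updated protocol is to be published before analysis.
- **Other treatment and Discussion.** "Any additional treatment will be recorded and included in the analyses" and "Any additional treatment or medication use will be monitored and included in the analyses". Neither sentence says in what role.

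**The concern.** The pandemic is an external event. The time a patient spends in therapy while it lasts is only partly external, because it also reflects how long the patient stayed. By the protocol's own rules a patient who recovers and leaves early accumulates less of it, and so does one who drops out. The covariate thus mixes calendar exposure with response and adherence.

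If the two therapies differ in how often or how soon patients leave, conditioning on this covariate compares DBT and ST patients who are alike in length of stay but unlike in prognosis. Part of a real difference can then be credited to the pandemic term, or a difference can appear where there is none. The adjusted contrast is no longer the effect of allocation, which is what intention to treat is meant to estimate.

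**Working it through.** **1. Yardstick: the plan's own power figure.** From Sample size: N = 200, d = 0.50, two-sided 0.05, ICC 0.05. The number of centres used there is not given; I assume 9 sites (Design names eight organisations, one at two places).

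- Patients per arm per centre: 200/(9 × 2) = 11.1
- Design effect: 1 + (11.1 − 1) × 0.05 = 1.506
- Effective n per arm: 100/1.506 = 66.4
- Standard error of the difference: √(2/66.4) = 0.174 SD
- Power: Φ(0.50/0.174 − 1.96) = 82.2%

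This reproduces the stated 82% (80.4% with 8 centres, 83.6% with 10).

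**2. Planned duration by arm.** From Table 2, taking the four-week pretreatment as one month: DBT 1 + 12 + 12 = 25 months; ST 1 + 18 + 6 = 25 months. Planned total time does not differ by arm. Actual time can, through early completion and dropout.

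**3. When bias arises.** Let A be arm, U unmeasured prognosis with an assumed weight of 0.6 on the outcome, and M the covariate scaled to within-arm variance 1, with M = aA + cU + error and no effect of M itself on the outcome. Within arm, the slope of the outcome on M is 0.6c, so the adjusted arm coefficient is off by

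bias = −a × c × 0.6.

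It is zero if a = 0 (arm does not shift the covariate) or c = 0 (covariate unrelated to prognosis). Under assumed values:

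- a = 0.2, c = 0.3: 0.2 × 0.3 × 0.6 = 0.036 SD
- a = 0.5, c = 0.5: 0.5 × 0.5 × 0.6 = 0.15 SD

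In simulation a true 0.50 becomes about 0.47 and 0.35, and the 82% power becomes about 77% and 52%.

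**4. The early-completion mechanism itself.** Simulation of 400,000 patients with no true arm difference. Outcome = 0.6U + 0.8 × noise, higher being worse. Pandemic onset is uniform from 12 months before entry to 24 months after. The course is 25 months, except that the best-prognosis patients, in an assumed arm-specific fraction, finish at 6 to 18 months. The document gives no such fractions.

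| Early completion ST / DBT | Arm estimate adjusted for actual time in treatment | Arm estimate adjusted for planned calendar overlap |
|---|---|---|
| 0% / 0% | 0.001 | 0.001 |
| 20% / 20% | 0.001 | 0.001 |
| 20% / 35% | −0.046 | −0.003 |
| 10% / 40% | −0.079 | −0.001 |

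The true value is 0 throughout; negative means ST looks better. By symmetry, swapping the rates reverses the sign. The two non-zero results are 0.046/0.174 = 0.26 and 0.079/0.174 = 0.45 of a standard error, or 9% and 16% of 0.50. Dropout was not simulated. It could tie short treatment to poor rather than good outcome, so it could offset or reverse these figures. The calendar measure stays at zero within simulation error.

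**The case against.** The strongest reply is that nothing is fixed. Time in treatment is given as an example, the definition is deferred, the analysis section calls its methods examples, and covariate definitions usually sit in an analysis plan. The other listed option, a pandemic/no-pandemic dummy, is sound if it is set by calendar date. All of this stands, and it limits the point to a listed option. It does not remove it: the commitment to control for the pandemic is firm, time in treatment is the only regression term named, and the article puts it beside the sound option without distinguishing them.

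It can also be said that the treatment comparison is, in the Discussion's words paraphrased, not the main aim. That bears on weight only, since comparative effectiveness is one of the four primary objectives.

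Four stronger readings are tempting and are not supported:

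- **That the plan will bias the comparison.** Bias needs a covariate that arm affects and that is tied to prognosis or lies on the causal path. Only *can bias* is supportable.
- **That additional treatment and medication will be regressors.** The text says only that they are included in the analyses. Costs counts medication and care contacts as cost items, other psychological treatment is a ground for exclusion from the completers analysis, and Clinical effectiveness names no post-randomisation covariate.
- **That the arms differ by six months by design.** "In DBT, the treatment phase has a maximum duration of 12 months" and "In ST, the treatment phase has a maximum duration of 18 months" might suggest it, but the COVID-19 section speaks of treatment, not the treatment phase, and the planned total is 25 months in both arms.
- **That the bias could reach 0.30 SD.** Multiplying an assumed arm difference of 0.2–0.6 SD by an assumed slope of 0.3–0.5 gives 0.06–0.30 SD. Neither input is in the document, and that product describes blocking a mediator, not conditioning on a consequence of response.

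**Conclusion.** The point holds in a narrow form. One of the two pandemic measures that the article offers is partly a consequence of response, dropout and arm, so using it in the primary DBT–ST comparison can bias the estimate and departs from intention to treat.

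Size and direction cannot be derived from the document. Assumed early-completion rates of 20% against 35%, and 10% against 40%, give about 0.05 and 0.08 SD; equal rates with no true arm difference give none. A wider grid of assumptions gives 0.04 to 0.15 SD. These are illustrations, not estimates. Even the modest values are worth avoiding, because a calendar-based measure serves the stated purpose without this problem. The unstated role of additional treatment and medication is a secondary wording matter.

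**What to change.** In the promised update:

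- Remove actual time in treatment as a pandemic adjustment in the primary comparison.
- Define exposure from calendar dates alone: for each planned assessment interval, the share that falls in a dated restriction period. Compute it for every analysed patient, whether or not still in treatment, from planned rather than achieved end dates.
- If the dummy is preferred, define it by calendar date too, not by whether the patient was in therapy.
- Add the exposure-by-arm interaction as a sensitivity analysis.
- Use actual time in treatment only descriptively or in sensitivity analyses.
- State that additional treatment and medication are reported by arm, costed or used in sensitivity analyses, and are not covariates in the primary effectiveness model.

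The cost is a few sentences. The dates should already be held, and assessments keep their planned timing after early completion, so no new data are needed. The choice should be fixed before analysis, as the article already intends.
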